**Fig. 3 Fig3:**
[figure not shown]
Intervention procedure using a real-time monitoring device

### Randomisation

Following the baseline study visit, all participants are randomised to one of the two study arms using 1:1 randomisation. The PASS 11.0 randomisation module will be used to ensure equal sizes of the two study groups. Each group will have 500 participants, and two groups of 500 random numbers will be generated for randomised grouping of the daily dose group and the event-driven group to ensure equality of the two medication dosing strategies within the intervention arm (Table 1).

**Table 1 Tab1:** Illustration of randomisation procedure

Serial number	Group^a^	Maximum deviation ratio to target (%)	Cumulative sample size of two groups (A, B)
1	B	0.1%	(0, 1)
2	A	0.0%	(1,1)
3	A	0.1%	(2, 1)
998	B	0.0%	(499, 498)
999	A	0.1%	(500, 499)
1000	B	0.0%	(500, 500)

^a^ A, intervention arm; B, control arm

Accordingly, both the PrEP daily FTC/TDF group and the event-driven FTC/TDF group will have 250 PrEP users randomly assigned to the intervention arm and 250 assigned to the control arm. Recruitment targets of four study sites were determined based on patient volume and are shown in Table 2.

**Table 2 Tab2:** Number of participants to be recruited at each site

Sites	Intervention arm	Control arm
Shenyang	185	185
Beijing	210	210
Shenzhen	45	45
Chongqing	60	60
Total	500	500

All study participants will be seen for a baseline study visit, followed up at 3 and 6 months, and fill an online self-administered questionnaire assessing sexual behaviours, psychological status, self-reported medication adherence, attitude and side effects towards PrEP use. Blood samples and dry blood spots will be collected and tested as previously described for the *CROPrEP* project [19]. Pills remaining will be counted at the 3- and 6-month follow-up visits, and refills will be provided to last until the next study or clinic visit. Participants will be required to return the real-time monitoring device provided by the program when the study is completed.

The program will incorporate locally trained community-based organizations (CBOs) serving MSM to recruit eligible participants for the study. CBO peer educators will be responsible for guiding the correct use of the monitoring device and will provide support services through social media platforms (WeChat, QQ). The study also offers incentives of US $10 upon completion of the enrolment visit and US $10 each at the 3- and 6-month visits (US $30 total) to compensate the time contributed by participants.

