### Trial design

This study is organized within the ongoing *CROPrEP* project, a multicentre, real-world prospective cohort study of daily or event-driven PrEP (emtricitabine/tenofovir disoproxil fumarate, TDF/FTC) among 1000 HIV-negative MSM most-at-risk of HIV infection in China. For the present study protocol, we randomly divided the 1000 *CROPrEP* study participants (500 from daily TDF/FTC group and 500 from event-driven TDF/FTC group in the *CROPrEP* study) into intervention and control arms in a 1:1 ratio (250 in intervention arm and 250 in control arm for each of the original *CROPrEP* study groups).

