### Sample size

We have powered the RCT to be able to detect meaningful changes in optimal adherence. Our estimates of outcome differences are based on our basic findings from our earlier pilot study with Chinese PrEP users, in which we found that proportions of adherence were 94% versus 86%, in intervention versus control patients after 6 months of the intervention. We will recruit 500 PrEP users per study arm. With the consideration of a two-sided alpha of 0.05 and 40% loss to follow-up of our study, we will have a 90.6% power at to detect specified differences in adherence between the two arms after intervention.

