### Statistical methods

Normal distribution continuous variables will be presented by means and standard deviations while non-normal distribution continuous variables will be presented by medians and interquartile ranges. For categorical variables, composition ratios and 95% confidence intervals will be used to describe the variables. Chi-square analysis will be used to assess differences between the study arms in HIV testing history, HIV self-testing (HIVST) characteristics, and high-risk behaviours. Multinomial logistic regression will be used to measure the outcome of real-time monitoring equipment on medication adherence.

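### Randomisation is stratified by dosing regimen, but the named adherence analysis mentions no regimen term and no by-regimen estimate

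*Protocol article*

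**What the plan says.** The Trial design section divides the 1000 participants, 500 on daily and 500 on event-driven TDF/FTC, into "250 in intervention arm and 250 in control arm for each of the original" study groups. The Randomisation section gives the mechanism: "two groups of 500 random numbers will be generated for randomised grouping of the daily dose group and the event-driven group". Regimen is therefore a stratification factor. Table 1 in that section illustrates a single sequence of 1000, which fits awkwardly with two lists of 500, but the text in both sections is explicit about the split within regimen.

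The Sample size section uses one pair of rates for both regimens together ("proportions of adherence were 94% versus 86%, in intervention versus control patients after 6 months") and one comparison of the two arms.

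The Statistical methods section gives one sentence to the effect analysis: "Multinomial logistic regression will be used to measure the outcome of real-time monitoring equipment on medication adherence". It names no covariate, no stratification and no analysis by regimen, and it excludes none of these.

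**The concern.** When allocation is balanced within a factor that predicts the outcome, differences between the levels of that factor no longer add to the chance variation of the arm comparison. An analysis that ignores the factor still counts those differences as error. Its standard error is then too large for the design, and its test rejects less often than the nominal level allows.

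There is also a question of interpretation. The Interventions section ties the reminders to a missed dose on a schedule, and the two regimens differ in their schedule. Whether the intervention works equally well in both is a natural question for this trial. A single combined estimate cannot answer it, and event-driven users make up half the sample.

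**Working it through.** **Inputs from the Sample size section.** "We will recruit 500 PrEP users per study arm"; "two-sided alpha of 0.05 and 40% loss to follow-up"; adherence 94% versus 86%. Evaluable per arm: 500 × (1 − 0.40) = 300.

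**Step 1: the plan's own power.** With the pooled variance under the null:

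- SE under the null = √(2 × 0.90 × 0.10 / 300) = 0.0245
- SE under the alternative = √((0.94 × 0.06 + 0.86 × 0.14) / 300) = 0.0243
- Power = Φ((0.08 − 1.96 × 0.0245) / 0.0243) = 0.906

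This reproduces the stated 90.6%. The figure is for the two arms overall and does not involve regimen.

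**Step 2: what leaving regimen out would cost.** The article gives no adherence by regimen, so a range is assumed:

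- control adherence is 86% + g in one regimen and 86% − g in the other;
- the odds ratio is the same in both regimens, set so that intervention adherence averages 94%;
- loss is equal, leaving 150 evaluable per regimen per arm;
- adherence is treated as a yes/no outcome, as in the sample size calculation.

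Formulas:

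- Unadjusted SE = √((0.94 × 0.06 + 0.86 × 0.14) / 300)
- Stratified SE = √(Σ p(1 − p) / (4 × 150)), summed over the four regimen-by-arm cells
- Power with the unadjusted SE = Φ((0.08 − 1.96 × unadjusted SE) / stratified SE)
- Power with the stratified SE = Φ(0.08 / stratified SE − 1.96)
- Actual alpha of the unadjusted test = 2[1 − Φ(1.96 × SE ratio)]

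| g (points) | Control rates, % | Intervention rates, % | Unadjusted SE | Stratified SE | Ratio | Power, unadjusted | Power, stratified | Actual alpha |
|---|---|---|---|---|---|---|---|---|
| 0 | 86 / 86 | 94.0 / 94.0 | 0.0243 | 0.0243 | 1.000 | 0.909 | 0.909 | 0.050 |
| 2 | 88 / 84 | 94.9 / 93.1 | 0.0243 | 0.0242 | 1.001 | 0.909 | 0.910 | 0.050 |
| 5 | 91 / 81 | 96.3 / 91.7 | 0.0243 | 0.0241 | 1.009 | 0.911 | 0.914 | 0.048 |
| 8 | 94 / 78 | 97.6 / 90.4 | 0.0243 | 0.0237 | 1.023 | 0.914 | 0.921 | 0.045 |
| 10 | 96 / 76 | 98.5 / 89.5 | 0.0243 | 0.0234 | 1.036 | 0.917 | 0.927 | 0.042 |
| 12 | 98 / 74 | 99.3 / 88.7 | 0.0243 | 0.0231 | 1.052 | 0.920 | 0.934 | 0.039 |

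The gap between regimens is 2g, so the last row is a 24-point gap. The first row shows 0.909 instead of 0.906 because these formulas use the unpooled variance. The alpha column takes the SE ratio at the planning rates, which approximates the ratio under the null.

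At the widest gap the power difference is 0.934 − 0.920 = 0.014, or 1.4 points. The SE excess of 5.2% corresponds to 1.052² = 1.107, about 11% in effective sample size.

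**Step 3: the same question in a logistic model.** These are fits to expected counts, with adherence as yes/no, a simplification of the multinomial model:

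| g (points) | Regimen term | Log odds ratio | Reported SE | z |
|---|---|---|---|---|
| 5 or 10 | no | 0.936 | 0.295 | 3.18 |
| 5 | yes | 0.950 | 0.297 | 3.20 |
| 10 | yes | 0.992 | 0.303 | 3.28 |

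Adding regimen makes the SE of the log odds ratio slightly larger, while the estimate moves further from zero. The gain therefore appears in z and in power, not as a narrower interval for the odds ratio. Without the term, the true standard deviation of the estimate is 0.293 (g = 5) or 0.287 (g = 10), below the reported 0.295. That is the same mild conservatism.

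**Step 4: what a single regimen can show.** Evaluable per arm within a regimen: 250 × 0.60 = 150. Power for 94% versus 86% = Φ((0.08 − 1.96 × √(0.18 / 150)) / √(0.1768 / 150)) = 0.638, about 64%.

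**The case against.** The strongest reply is that the article is silent on this point and contradicts nothing. Choosing a regression model is compatible with arm, regimen and site terms, and a condensed article often leaves covariates and subgroup analyses to a fuller plan. This stands in part. A reader might infer that the trial will pool the regimens without adjustment and so hide a difference between them. The text does not say so, and nothing in it rules out adjusted or by-regimen results. What remains is that the article describes the stratified allocation in detail, names the effect analysis, and does not connect the two.

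The second reply is that the effect is small, and this stands. A reader might assume much wider gaps, such as 95% versus 60% or 90% versus 40%. The variance ratios would then be 0.82 and 0.73, the latter a gain of up to 38% in effective sample size. Those pairs average 77.5% and 65%, whereas the planning rates average (94 + 86) / 2 = 90%. With a 90% average the most extreme split is 100% and 80%, giving a ratio of ((0 + 0.16) / 2) / 0.09 = 0.89. Larger losses are therefore not supported for the planning outcome.

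Third, a reader might expect adjustment to narrow the interval for the odds ratio in the planned model. Step 3 shows that it does not.

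Fourth, a reader might extend the argument to site, because Table 2 has equal arm numbers in each city. The article calls these recruitment targets and describes separate random lists only for regimen, so site-stratified allocation is not stated.

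**Conclusion.** The point holds as a modest matter of efficiency and interpretation. It is not a threat to validity. Allocation is stratified by regimen, and the named analysis mentions no regimen term and no by-regimen estimate. If regimen were omitted, the unadjusted SE of the risk difference would be about 0% to 5% too wide, the actual alpha 0.050 to 0.039, and the power loss at most about 1.4 points. These figures rest on the planning rates of 86% and 94%, 40% loss spread evenly, a common odds ratio, and an assumed control-arm gap of 0 to 24 points. There is no bias on the risk-difference scale, and no cost if the regimens have equal adherence. The stated power of 90.6% is correct for the comparison it describes.

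**What to change.** State in the Statistical methods section that regimen enters the primary adherence model as the randomisation stratification factor. Report a risk difference alongside it, either Mantel-Haenszel over regimen or standardised over regimen from the model, since that is the scale on which the stratification gains precision.

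Pre-specify as secondary the effect within each regimen, with confidence intervals and an arm-by-regimen interaction. Present these as estimates: power within one regimen is only about 64% for the planned difference, so a non-significant result in one regimen should not be read as no effect.

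Site may be added as a covariate. If allocation was in fact stratified by site, the article should say so.

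The cost is a sentence or two of analysis text. Regimen is known for every participant at randomisation, so no extra data and no change in sample size are needed.

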### Laboratory procedure

The laboratory testing procedures and parameters are described in the published protocol of the *CROPrEP* project [19]. MSM who are enrolled in the study and later screen as HIV positive will be instructed to discontinue PrEP and visit the local study hospital for HIV confirmation.

### Data collection and management

The study questionnaire will be administered via a specialised online platform (Gold Data Technologies, Sichuan, China). Trained staff will collect data on remaining pill counts and verify test results.

CBO peer educators will instruct study participants on use of the real-time monitoring device at the baseline study visit and throughout follow-up using related images and videos in order to avoid overestimates (opening the container without removing pills) or underestimates (multiple pills removed during one opening of the monitoring device) of actual medication adherence. The monitoring device battery is sufficient to run in standby mode for 45 days after a 2-h charge.

### Study endpoints

Medication adherence refers to the degree to which a patient complies with the doctor’s prescription to complete the treatment plan. It involves taking medication regularly, not forgetting to take medication, and taking medication at the correct time, i.e., taking medicine according to the prescribed timing, dosage, and administration instructions. PrEP medication adherence will be measured via self-report questionnaires and pill counts as well as drug concentration test results. Details on the study endpoints are shown in Table 3.

**Table 3 Tab3:** Study endpoints

**Medication adherence scores** - The proportion of self-reported number of pills taken among the number of pills prescribed by the doctor. - The proportion of the counted number of pills taken among the number of pills prescribed by the doctor. - The proportion of pills taken as calculated by remote real-time monitoring equipment among the number of prescribed pills by the doctor. Scores will be classified as high medication adherence (≥90%), intermediate medication adherence (≥60 and < 90%), or low medication adherence (< 60%).	
**Blood medicine concentration monitoring (TDF/FTC)** Blood TDF/FTC concentration will be classified as high medication adherence (≥90% concentration), intermediate medication adherence (≥60 and < 90%), or low medication adherence (< 60%).	

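### Table 3 grades blood drug concentration with pill-proportion limits (90%/60%), states no reference for the percentage, and uses one rule for daily and event-driven users

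*Protocol article*

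**What the plan says.** All of this is in the protocol article.

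- **Study endpoints, text.** Drug concentration is listed as an adherence measure beside the other two: "PrEP medication adherence will be measured via self-report questionnaires and pill counts as well as drug concentration test results".
- **Study endpoints, Table 3, pill scores.** Each of the three scores has a stated denominator, for example "The proportion of the counted number of pills taken among the number of pills prescribed by the doctor". The grading begins "Scores will be classified as high medication adherence (≥90" per cent, with 60% as the border between intermediate and low.
- **Study endpoints, Table 3, drug level.** "Blood TDF/FTC concentration will be classified as high medication adherence (≥90% concentration", followed by the same 60% border. No reference level, analyte-specific limit or specimen is given.
- **Trial design.** The participants are "500 from daily TDF/FTC group and 500 from event-driven TDF/FTC group". Table 3 does not separate them.
- **Randomisation.** "Blood samples and dry blood spots will be collected and tested as previously described" for the parent cohort, so two kinds of specimen exist.
- **Laboratory procedure.** "The laboratory testing procedures and parameters are described in the published protocol of the" parent project. The sentence covers laboratory work and does not mention adherence grading.

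**The concern.** The pill limits are meaningful because a pill score is a fraction: 90% means nine tenths of the prescribed pills. A concentration is an amount per volume and has no natural 100%. Two people with the same intake can have different levels, so even with a reference, 90% of a level does not correspond to 90% of pills.

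The event-driven half adds a second difficulty. The Study endpoints section defines adherence as following the prescription. Someone on an event-driven regimen who has had no recent event can have followed it fully and carry little drug. A common percentage rule would grade that person low. In this group the level mixes adherence with recent sexual activity.

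The Discussion says that self-report and pill counting tend to overstate adherence. The device treats each opening as a dose taken (Real-time monitoring equipment), and the Discussion says real-time medication status is unknown in controls. Drug level is thus the one biological check that covers both arms, and misgrading in both arms would shrink a real difference on it.

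**Working it through.** **1. The plan's own figure.** Inputs from Sample size: 94% vs 86%, 500 per arm, 40% loss, two-sided alpha 0.05.

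- Analysed per arm: 500 × (1 − 0.40) = 300.
- Pooled proportion: 0.90. Standard error under the null: √(0.90 × 0.10 × 2/300) = 0.02449.
- Standard error under the alternative: √((0.94 × 0.06 + 0.86 × 0.14)/300) = 0.02428.
- Power: Φ((0.08 − 1.96 × 0.02449)/0.02428) = Φ(1.318) = 90.6%.

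This matches the stated figure. The point disputes no number in the sample size.

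**2. The two rules in Table 3 side by side.**

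| | Pill scores | Drug level |
|---|---|---|
| Quantity | pills taken | concentration |
| Denominator | pills prescribed | not stated |
| Limits | 90%, 60% | 90%, 60% |
| Specimen | not applicable | blood or dried spot, not stated |
| Daily vs event-driven | denominator follows the individual prescription | one rule, no adjustment |

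**3. Misgrading of fully adherent daily users (illustration).** None of these inputs is in the documents. Assume log-normal levels, between-person CV of 20% to 60%, and a reference at the median of fully adherent users. With s = √ln(1 + CV²):

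- P(below 90%) = Φ(ln 0.9 / s)
- P(below 60%) = Φ(ln 0.6 / s)

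| CV | s | misses high | graded low |
|---|---|---|---|
| 20% | 0.198 | 29.7% | 0.5% |
| 30% | 0.294 | 36.0% | 4.1% |
| 40% | 0.385 | 39.2% | 9.2% |
| 60% | 0.555 | 42.5% | 17.8% |

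**4. Dependence on the unstated reference.** Hold the CV at 30% and set the reference at 100%, 70% or 50% of the fully adherent median. The cut for high then lies at 0.90, 0.63 or 0.45 of that median. The share of fully adherent users graded high is 1 − Φ(ln(cut)/0.294), which gives 64%, 94% and 99.7%.

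**5. Dilution of an arm difference.** Add one more assumption: users who are not highly adherent have a median at 70% of the reference. Their chance of being graded high is 1 − Φ(ln(0.9/0.7)/s), which is 10.2% at CV 20% and 32.5% at CV 60%. A true difference in the share highly adherent is multiplied by:

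- CV 20%: 0.703 − 0.102 = 0.60
- CV 60%: 0.575 − 0.325 = 0.25

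**6. Event-driven users.** No calculation is possible, because the article gives no distribution of events or of time since the last dose. The direction follows from the definition: without a recent event, the level is low whatever the adherence.

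**The case against.** The strongest reply is that the missing detail may sit in the parent project's published protocol, to which the article sends the reader for laboratory procedures and parameters. A condensed article need not repeat an assay calibration, and the wording in Table 3 may be shorthand for the level expected at 90% of doses. This stands in part. A reader might infer that the measure cannot be graded validly at all, or that a reference must be picked after the data are seen. The documents do not support either inference, because a reference may already exist. However, Table 3 does not leave the grading to another document. It prints a three-level rule, and a reference found elsewhere would not by itself turn a percentage of a level into a percentage of pills, nor separate the two regimens.

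Other stronger readings also fail:

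- **The only objective endpoint.** Trained staff count the remaining pills in both arms, and the device logs openings in the intervention arm. The accurate description is the only biological measure available in both arms.
- **Limits copied from the pill scores.** The article shows that they are identical. It does not show how they were chosen.
- **An 8-point effect swamped, or the trial underpowered.** Sample size does not say which adherence measure the 94% and 86% describe.

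It is also fair to say that the variation between people is not described in the documents. The percentages above therefore illustrate the mechanism and do not estimate error in this trial.

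**Conclusion.** The concern holds as a badly fixed grading rule. Table 3 applies limits made for a proportion to a quantity that is not one, names neither reference nor specimen, and treats 500 daily and 500 event-driven users alike.

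The size cannot be known from the documents. Over the assumed CV range and with the reference at the fully adherent median, roughly 30% to 42% of fully adherent daily users would miss the high grade and 0.5% to 18% would be graded low. A lower reference would cut these shares sharply, so the choice of reference largely decides the grading. The effect on an arm comparison is dilution. Its amount rests on the further assumption in step 5.

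**What to change.** In Table 3:

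1. Name the analyte and the specimen to which the drug-level rule applies.
2. Analyse daily and event-driven users separately, using the regimen groups within which participants are already randomised.
3. **Daily users.** Replace the percentage limits with assay concentration thresholds that correspond to doses taken, fixed before any outcome data are seen. Cite the parent project's calibration if it provides one. If it does not, compare log concentration between arms as a continuous outcome.
4. **Event-driven users.** Compare all randomised participants on drug detection or level as a measure of exposure, and do not label a low level as low adherence. Give results by reported recent event only as a supportive analysis. That subset is selected after randomisation and by self-report, so it no longer carries the protection of randomisation.

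The change is one of wording, because the samples are already planned. The drug-level endpoint would no longer yield a single pooled three-level category. Each regimen comparison would also be less precise: 250 per arm instead of 500, or 150 instead of 300 after the planned 40% loss, which widens standard errors by √2, about 1.41.
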